| Secondary study objectives:
1. To evaluate other anti-tumor efficacy endpoints of high-dose aumolertinib:
Intracranial: intracranial progression-free survival (iPFS), intracranial objective response rate (iORR), duration of intracranial response (iDoR), and intracranial disease control rate (iDCR);
Systemic: objective response rate (ORR), overall survival (OS), duration of response (DoR), and disease control rate (DCR).
2. To evaluate the safety of high-dose aumolertinib.                                                                                                                                                                                                                                                                                                                                                                                                                                                                                                                                    |                                                                 |                                                                                                                             |                                                                                                                                                                                                                                                                                                                                                                                                                                                                  |                  |                  |  |                  |                                                                                                                                                                                                                                                                                                                                                      |                                                                 |  |                                                                                                                                                                                                                                                                                                                                                                                                                                                                  |

**Exploratory study objectives:**

To explore the dynamic change of blood gene mapping before and after treatment and its correlation with efficacy.

**Inclusion criteria:**

A subject must meet all the following inclusion criteria in order to be enrolled in this study:

1. Age  $\geq 18$  years old.
2. Histologically or cytologically confirmed NSCLC, which is confirmed by imaging as advanced NSCLC with metastases to brain parenchyma (including stage IV patients who are newly diagnosed or have relapsed after previous surgical treatment; according to the AJCC 8th edition lung cancer staging criteria).
3. Confirmed as EGFR-sensitive mutations in tumor tissue samples or blood samples by local laboratory (including exon 19 deletion or L858R, either existing alone or co-existing with other EGFR site mutations). If the tumor tissue is not available or the patient does not accept tissue biopsy, a blood sample is acceptable.
4. Have not received any systemic anti-tumor treatment after the diagnosis of advanced NSCLC with metastases to brain parenchyma. For patients who have received local treatment, the lesion within the scope of the local treatment cannot be used as the target lesion unless the lesion has progressed.
5. Patients with at least 1 extracranial target lesion (measurable lesions that have not undergone local treatment such as irradiation or have shown definitive after local treatment, with a baseline longest diameter  $\geq 10$  mm (or  $\geq 15$  mm for lymph nodes)) and at least 1 intracranial lesion (with a baseline longest diameter  $\geq 5$  mm).
6. The brain condition is stable or that were controlled with anticonvulsants or dexamethasone at a maximum dose of 5 mg daily before the study treatment.
7. The Eastern Cooperative Oncology Group (ECOG) performance status score is 0 or 1, and has not deteriorated at least 2 weeks before the study treatment, and the expected survival period is not less than 3 months.
8. Female patients of childbearing potential are willing to take appropriate contraceptive measures and should not breastfeed from signing the informed consent to 6 months after the last dose of study treatment; male patients are willing to take barrier contraception (i.e., condoms) from signing the informed consent to 6 months after the last dose study treatment.
9. Female patients of childbearing potential must have a negative serum or urine HCG test within 7 days before enrollment in the study, and they must be non-lactating.
10. The subject voluntarily participates and signs the informed consent form in writing.

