### 9.1.3.4 Follow-up of patients after any disease progression

At the time of disease progression assessment, 3 sets of assessments will be performed in this study: systematic assessment, intracranial assessment, and extracranial assessment. During the overall assessment, extracranial and intracranial target lesions (no more than 5 target lesions in the whole body and at least one target lesion in the skull) will be selected according to RECIST 1.1, and then the selected intracranial and extracranial lesions will be subjected to separate intracranial and extracranial response evaluation according to the RECIST 1.1. There is no need to select additional intracranial or extracranial target lesions. See Table 3 for systemic, intracranial, and extracranial disease progression, subsequent anti-tumor therapies, and recommendations for data collection.

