response (PR), stable disease (SD), and progressive disease (PD). The analysis of the primary endpoint of this study will be based on the tumor response assessment made by the investigator as per RECIST 1.1, and the investigator will also manage the subjects based solely on the assessment results, unless medically contraindicated or faced with force majeure factors (such as update of the examination instrument by the study site). Baseline CT or MRI assessments of the chest, abdomen, and brain tissues must be performed within 28 days before the start of study treatment (not subject to the time of signing the ICF), and should be performed as close as possible to the start of study treatment. The investigator should perform additional imaging examinations based on subjects' signs and/or symptoms. The subsequent follow-up assessments should be performed using the method (CT/MRI) that is the same as that for baseline assessment. All enrolled subjects must have brain metastases as target lesions, and baseline imaging assessment of the brain must be performed, with MRI (enhanced) as the preferred examination method. Bone scans should be performed if there are indications for bone metastases (results within 3 months are acceptable), and positive sites found by bone scans should be confirmed by CT/MRI/X-ray. Only confirmed lesions can be recorded as non-target lesions. Subsequently, the bone metastases should be followed up by the same examination method as at baseline. During the study, bone scans may be added as needed. During the treatment period, tumor response assessment will be performed once every 8 weeks ( $\pm 1$  week) until progressive disease assessed by investigator per RECIST 1.1 (see Section 12.1.3 or 9.1.3.4). Tumor assessments should be performed according to the study plan whenever possible. If subjects are assessed at a time point beyond the scheduled time window ( $\pm 1$  week) and no progressive disease occurs, they should undergo subsequent assessments at the pre-specified time points whenever possible while continuing study treatment. If tumors are suspected at any other sites, the corresponding imaging examinations should be performed at the relevant sites. To achieve progression on the basis of the non-target lesion(s), there must be an overall level of substantial worsening in non-target lesion(s) such that, even in the presence of SD or PR in the target lesion(s), the overall tumor burden has increased sufficiently to merit discontinuation of treatment. A modest increase in the size of one or more non-target lesions is generally not sufficient to qualify for progression; therefore, it is uncommon to define overall tumor progression only with changes in non-target lesions in the face of SD or PR of target lesions. At each visit, objective tumor response will be assessed as per RECIST 1.1, and classified into CR, PR, SD, and PD. For the assessment of target lesion progression, the smallest lesion size in the entire course of treatment should be taken as reference, and an increase meeting the criteria will qualify for PD. If no progressive disease occurs, tumor response (CR and PR) and stable disease (SD) should be evaluated taking baseline lesion(s) as reference.

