#### **12.1.4 Duration of response (DoR)**

DoR is defined as the time from the date of first compliance with response to the date of PD or death due to any cause. The end date of the response should be consistent with the date of the endpoint PFS. The start of DoR is defined as the latest date of the visit at which PR or CR criteria are first met. If a patient does not progress after a response, the censored time for PFS will be used for DoR.

Intracranial duration of response (iDoR) and systemic duration of response (DoR) will be assessed separately.

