### Special cases

- For TLs that can be measured in 2 or 3 dimensions, the longest diameter will be always reported. For pathological lymph nodes that can be measured in 2 or 3 dimensions, the short axis will be always reported.
- If the thickness of slices used in CT/MRI is  $> 5$  mm, the minimum size of measurable lesions at baseline should be twice the slice thickness on baseline scan.
- If the lesion disappears completely, the longest diameter should be recorded as 0 mm.
- If the TL splits into 2 or more parts, the sum of diameters of these parts should be recorded.
- If 2 or more TLs are combined, the sum of diameters of the combined lesions should be recorded, and the diameter of other lesions should be recorded as 0 mm.
- If the TL is believed to be present and is faintly seen but too small to measure, a default value of 5 mm should be assigned. If accurate measurements can be obtained, they should be recorded, even if they are below 5 mm.
- If the TL is too large to be accurately measured, an estimated value of the lesion size should be given.
- When any intervention is made to the TL during the study, such as radiotherapy, embolization, and surgery, the size of the TL should still be given where possible.

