**Table 2. Overall response of target lesions**

|                                 |                                                                                                                                                                                                                                                                                            |
|---------------------------------|--------------------------------------------------------------------------------------------------------------------------------------------------------------------------------------------------------------------------------------------------------------------------------------------|
| Complete response (CR)   | Disappearance of all target lesions from baseline. Any pathological lymph nodes selected as TLs must have a short axis of $< 10$ mm.                                                                                                                                                       |
| Partial response (PR)    | At least a 30% decrease in the sum of diameters of TLs, taking as reference the baseline sum diameters.                                                                                                                                                                                    |
| Stable disease (SD)      | Neither sufficient shrinkage to qualify for PR nor sufficient increase to qualify for PD.                                                                                                                                                                                                  |
| Progressive disease (PD) | At least a 20% increase in the sum of diameters of TLs, taking as reference the smallest sum on study (this includes the baseline sum if that is the smallest on study). In addition to the relative increase of 20%, the sum must also demonstrate an absolute increase of at least 5 mm. |
| Inevaluable (NE)         | Only relevant TLs are not assessed or not evaluable or have lesion intervention.
Note: If the sum of diameters meets the criteria of PD, the lesion is not inevaluable and should be classified as a PD.                                                                                |

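### After intracranial complete response, a brain target that returns measurably below 5 mm is not progression while a fainter one is, and the minimum size of a brain target is contradictory

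*Protocol*

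**What the plan says.** **Size of a brain target.** Criterion 5 (Synopsis and section 7.1) asks for an extracranial target lesion "and at least 1 intracranial lesion (with a baseline longest diameter" of at least 5 mm). Section 10.2.1 states "All enrolled subjects must have brain metastases as target lesions", and section 9.1.3.4 specifies "no more than 5 target lesions in the whole body and at least one target lesion in the skull". Appendix D sets measurability at 10 mm (2.1) and admits only measurable lesions as targets, at most two per organ (2.4, 4.2.1). It makes no exception for the brain. Section 12.4.1 defines the cEFR as the part of the FAS with at least one measurable brain lesion.

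**Progression of targets.** Under 9.1.3.4, "the selected intracranial and extracranial lesions will be subjected to separate intracranial and extracranial response evaluation according to the RECIST 1.1". Appendix D Table 2 requires a 20% rise over the smallest sum, and "the sum must also demonstrate an absolute increase of at least 5 mm". There is no intracranial version.

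**Recording small lesions.** Under the special cases in Appendix D 4.2.1, a lesion that has vanished is entered as 0 mm. One that is seen but cannot be measured gets a default of 5 mm. The section adds: "If accurate measurements can be obtained, they should be recorded, even if they are below 5 mm".

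**Endpoints.** iPFS ends at intracranial progression or death (12.1.2). For response duration, 12.1.4 says "DoR is defined as the time from the date of first compliance with response to the date of PD or death due to any cause", and iDoR is assessed separately on that definition.

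**The concern.** The brain-lesion entry size is 5 mm, but the progression rule applied to brain lesions is the general one, whose absolute floor is also 5 mm. For a very small target the floor is as large as the lesion. After intracranial complete response nothing is left to measure a percentage against, so the floor is the whole test.

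iPFS and iDoR are named secondary endpoints of a brain-metastasis trial. Investigators assign progression at site from this text, so an unclear or perverse rule goes straight into the event dates.

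**Working it through.** The plan states no figure on this point, so there is none to reproduce. The check applies its rules to small sums.

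**1. Which rule applies to a 5 to 9 mm brain lesion?**

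| Text followed | Status of the lesion | Progression rule |
|---|---|---|
| Criterion 5 with 9.1.3.4 and 10.2.1 | must serve as target if it is the only brain lesion | Table 2: +20% and +5 mm |
| Appendix D 2.1, 2.4, 4.2.1 | not measurable, hence non-target | Table 3: unequivocal progression, no mm floor |

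Section 12.4.1 fits the second row: a subset defined by a measurable brain lesion implies that some FAS patients may have none. The two rows cannot both hold.

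**2. Target threshold.** With N the smallest intracranial target sum, progression needs max(1.2 × N, N + 5 mm). The floor governs while 0.2 × N < 5, that is, N < 25 mm.

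| N (mm) | Threshold (mm) | Rise over N |
|---|---|---|
| 3.5 | 8.5 | +143% |
| 5 | 10 | +100% |
| 8 | 13 | +62.5% |
| 10 | 15 | +50% |
| 15 | 20 | +33% |
| 20 | 25 | +25% |
| 25 | 30 | +20% |

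The 3.5 mm row is a lone 5 mm target after the smallest partial response (0.7 × 5). Its threshold of 8.5 mm is 8.5/5 = 1.70 times baseline.

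**3. Illustrative delay against the 20% rule alone.** Assume exponential growth, with diameter doubling in 3 × VDT, where VDT is the volume doubling time. The lag is 3 × VDT × log2(threshold / (1.2 × N)).

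- N = 5 mm: 3 × log2(10/6) = 2.21 VDT
- N = 10 mm: 3 × log2(15/12) = 0.97 VDT

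| Assumed VDT | N = 5 mm | N = 10 mm |
|---|---|---|
| 30 days | 9.5 weeks | 4.1 weeks |
| 60 days | 19.0 weeks | 8.3 weeks |
| 120 days | 37.9 weeks | 16.6 weeks |

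The doubling times are not in the protocol. The lag arises only when growth of the target is the sole sign of intracranial progression.

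**4. After intracranial complete response (N = 0).** The threshold is 0 + 5 = 5 mm.

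| Single returning target | Recorded | Increase | Result |
|---|---|---|---|
| measured accurately | 4.9 mm | 4.9 < 5 | not progression |
| visible but not measurable | 5 mm (default) | 5 ≥ 5 | progression |

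Appendix D 4.4 does not class a returning baseline lesion as new, and Table 2 has no reappearance rule. The better-defined relapse is left unscored and the vaguer one is scored. A 10 mm brain target that vanished and came back at 4.9 mm is treated the same way, so this step does not depend on step 1.

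**The case against.** The strongest reply is that the protocol chose RECIST 1.1 and states its progression rule consistently. The floor has a purpose: without it, 5 to 6 mm would be progression, a 1 mm change on scans where CT slices may be up to 5 mm thick. The 20% comparator in step 3 is therefore severe. Starting the clock at a 3 mm rise instead gives 3 × log2(10/8) = 0.97 VDT for the 5 mm lesion, less than half of 2.21. New lesions, non-target progression and death all end iPFS without any floor. Both endpoints are secondary and descriptive. All of this stands, and it is why the floor as such is not called an error here.

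It can also be said that Appendix D 4.4 is silent on returning lesions, so a site might call one new. Silence does not make that the rule, and Table 2 as written gives the result in step 4.

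A further objection is that 9.1.3.4 ties intracranial progression to subsequent treatment, so editing Table 2 would reach into management. That is a fair reason to confine the change to endpoint derivation.

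**Conclusion.** Two things hold. First, the passages on the minimum size of a brain target contradict each other and decide which progression rule a 5 to 9 mm lesion follows. Second, after intracranial complete response the stated rules leave a single measured regrowth below 5 mm unscored while scoring a fainter one, so iPFS and iDoR can continue through a definite relapse. The second rests only on the recording rules and Table 2.

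Stronger readings are tempting but not supported:

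- That brain targets simply enter at 5 mm: this is one side of the contradiction.
- That a small lesion must double: this fits only a lone 5 mm target that never shrank.
- That a lesion must regrow to baseline size after complete response: a faint reappearance counts as 5 mm at once.
- That iPFS and iDoR are overstated: upward bias is possible, but the protocol gives neither the distribution of brain-lesion sizes nor the share of progressions seen only as target growth. The lags in step 3 illustrate a mechanism and do not estimate a bias.

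The point merits correction but does not threaten the trial's main conclusion.

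**What to change.** 1. Reconcile criterion 5 (Synopsis and 7.1), 9.1.3.4 and 10.2.1 with Appendix D 2.1, 2.4 and 4.2.1 and with the cEFR definition in 12.4.1, so that one minimum size for a brain target applies throughout and the progression rule for smaller brain lesions is explicit.
2. In the iPFS and iDoR definitions (12.1.2 and 12.1.4), state that unequivocal reappearance of a brain target lesion after intracranial complete response counts as intracranial progression on that scan date, whatever its measured size. State that this serves endpoint derivation only and leaves treatment decisions unchanged.

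The cost is a wording alignment and one derivation rule using scans and diameters already collected. It also means keeping the derived date distinct from the assessment used for management. The downside is a few earlier progression dates and slightly shorter iPFS and iDoR.

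Reporting both endpoints by baseline brain-target size (below 10 mm, and 10 mm or more) is optional. Replacing the 5 mm floor with a smaller one, such as 3 mm, is not recommended: nothing in the protocol supports that value, and it would trade delay for false progression from reading error.

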**Exclusion criteria:**

A subject will not be eligible for inclusion in this study if any of the following criteria apply:

1. Treatment with any of the following:
  - a. Previously received EGFR tyrosine kinase inhibitor (EGFR-TKI) treatment (such as erlotinib, gefitinib, icotinib, afatinib, osimertinib, and aumolertinib);
  - b. The patient has undergone major surgery (such as craniotomy, thoracotomy, or laparotomy) within 4 weeks before the first dose of the investigational medicinal product, or undergone minor traumatic surgery (biopsy, bronchoscopy, and thoracic drainage) within 7 days before the first dose of the investigational medicinal product. Major surgeries are defined as Grade 3 and Grade 4 surgeries specified in the "Administrative Measures for Clinical Application of Medical Technology" implemented from Nov. 1, 2018 in Appendix H;
  - c. Patients who have received local radiotherapy (palliative bone radiotherapy for non-target lesions) within 2 weeks before the first dose of the investigational medicinal product; patients who have received more than 30% of bone marrow irradiation (see Appendix I for the calculated area of bone marrow) or extensive radiotherapy within 4 weeks before the first dose of the investigational medicinal product; patients who have received whole brain radiotherapy for this disease before enrollment;
  - d. Recurrence within 6 months after adjuvant or neoadjuvant treatment for early lung cancer; if there is both neoadjuvant therapy and adjuvant therapy, the adjuvant treatment time will be used for calculation;
  - e. Within 14 days before the first dose of the investigational medicinal product, traditional Chinese medicines and their preparations with anti-tumor effect or adjuvant anti-tumor effects have been used (see Appendix E for the list of drugs);
  - f. Presence of pleural/abdominal effusion requiring clinical intervention (patients who do not require drainage of the effusion or are stable for more than 2 weeks after drainage of the effusion are eligible); presence of pericardial effusion (patients with small amount of pericardial effusion who are stable for 2 weeks or more are eligible). If anti-tumor drugs are used locally (e.g., via intrapleural infusion) during drainage, patients are only eligible with a washout of at least 5 half-lives or 21 days (whichever is shorter) prior to the first dose of study treatment;
  - g. Previously treated with drugs that are strong inhibitors or strong inducers of CYP3A4, or treated with

- CYP3A4 sensitive substrate drugs with a narrow therapeutic window, within 7 days prior to the first dose of investigational medicinal product; or requiring to continue the treatment with these drugs during the study (see Appendix E for the list of these drugs);
- h. Receiving drugs known to prolong the QT interval or that may cause torsade de pointes, or requiring to continue the treatment with these drugs during the study (see Appendix E for the list of drugs and washout times);
  - i. Having participated in another clinical trial within 4 weeks or been still within 5 half-lives of the investigational medicinal product in another clinical trial before the first dose of this investigational medicinal product, whichever is longer (except for screening failure).
2. Histologically or cytologically confirmed mixed SCLC and mixed NSCLC, large cell neuroendocrine carcinoma and sarcomatoid carcinoma.
  3. At the beginning of study treatment, those with residual toxicity from prior anti-tumor treatment greater than CTCAE Grade 1 that cannot be alleviated, with the exception of hair loss and Grade 2 neurotoxicity from prior anti-tumor treatment. History of intracranial hemorrhage not related to tumor.
  4. History of other primary malignant tumors, except for the following:
    - a. Radically treated malignancies that have been inactive for  $\geq 5$  years prior to study enrollment and have a very low risk of recurrence;
    - b. Adequately treated non-melanoma skin cancer or lentigo maligna without evidence of disease recurrence;
    - c. Adequately treated carcinoma *in situ* without evidence of disease recurrence.
  5. Diagnosis of meningeal metastasis through clinical symptoms or imaging or cerebrospinal fluid, or brain parenchymal metastasis combined with meningeal metastasis.
  6. Patients who are allergic to MRI contrast agent gadolinium or who cannot tolerate MRI examinations (such as patients with pacemakers or metals in the body).
  7. Any serious or poorly controlled systemic disease, such as poorly controlled hypertension, active bleeding diathesis, or active infection, as judged by the investigator. There is no need to check for chronic diseases.
  8. Clinically serious abnormal gastrointestinal function, which may affect the intake, transport or absorption of drugs, such as inability to take drugs orally, uncontrollable nausea or vomiting, history of extensive gastrointestinal resection, uncured recurrent diarrhea, atrophic gastritis, uncured gastric diseases that require proton pump inhibitors for a long time, Crohn's disease, and ulcerative colitis.
  9. Hepatic encephalopathy, hepatorenal syndrome, or cirrhosis.
  10. Any of the following cardiac findings:
    - a. Mean QT interval corrected by Fridericia (QTcF)  $> 470$  msec from 3 repeated measurements of electrocardiogram (ECG) at rest;
    - b. Any clinically significant abnormalities in rhythm, conduction, or ECG morphology determined by the investigator (e.g., complete left bundle branch block, third-degree atrioventricular block, second-degree atrioventricular block, and PR interval  $> 250$  msec), as indicated by ECG at rest;
    - c. Presence of any factor that increases the risk of QTc prolongation or arrhythmic events, such as cardiac failure, hypokalemia, congenital long QT syndrome, family history of long QT syndrome, or unexplained sudden death of immediate family members under 40 years of age, or any concomitant medications known to prolong QT interval;
    - d. Left ventricular ejection fraction (LVEF)  $< 50\%$ .
  11. Insufficient bone marrow reserve or organ function, meeting any of the following laboratory test limits (no corrective treatment within 1 week before blood collection for laboratory tests):
    - a. Absolute neutrophil count  $< 1.5 \times 10^9/L$ ;
    - b. Platelet count  $< 100 \times 10^9/L$ ;
    - c. Hemoglobin  $< 90$  g/L ( $< 9$  g/dL);
    - d. Alanine aminotransferase  $> 2.5 \times$  upper limit of normal (ULN) in the absence of demonstrable liver metastases; alanine aminotransferase  $> 5 \times$  ULN in the presence of liver metastases;
    - e. Aspartate aminotransferase  $> 2.5 \times$  ULN in the absence of demonstrable liver metastases; aspartate aminotransferase  $> 5 \times$  ULN in the presence of liver metastases;
    - f. Total bilirubin  $> 1.5 \times$  ULN in the absence of demonstrable liver metastases, or total bilirubin  $> 3 \times$  ULN in the presence of Gilbert's syndrome (unconjugated hyperbilirubinemia) or liver metastases;
    - g. Creatinine  $> 1.5 \times$  ULN and creatinine clearance  $< 50$  mL/min (calculated by Cockcroft-Gault formula); creatinine clearance should be determined only when creatinine is  $> 1.5 \times$  ULN;
    - h. Serum albumin (ALB)  $< 28$  g/L;
  12. Female subjects who are pregnant and lactating or plan to become pregnant during the study period.

13. History of interstitial lung disease, drug-induced interstitial lung disease, radiation pneumonitis requiring steroid therapy, or any evidence of clinically active interstitial lung disease.
14. History of hypersensitivity to any active or inactive ingredients of aumolertinib or drugs of similar chemical structure or the same class as aumolertinib.
15. Patients with eye disorders that may increase the safety risk of patients as judged by the investigator (especially severe dry eye syndrome, dry keratoconjunctivitis, severe exposure keratitis, or other diseases that may increase epithelial damage) and require surgery or eye abnormalities that are expected to require surgery during the study.
16. Patients who may have poor compliance with the procedures and requirements of the study as judged by the investigator, such as patients who have a clear history of neurological or mental disorders (including epilepsy or dementia), or patients who are currently suffering from mental disorders.
17. Patients with any conditions that may jeopardize patient safety or interfere with study assessments as judged by the investigator.

